### Study organization

All serious adverse events and all unexpected and related or possibly related adverse events will be reported to the internal review board of the Medical Faculty and the University Hospital Dresden. Regular checks for plausibility and protocol adherence will be done according to good clinical practice (GCP) guidelines. Two independent experts in the field that are not part of the study group serve on the study’s data safety and monitoring board (DSMB) to ensure adherence to the study protocol, quality of data collection and processing as well as safety issues related to the study.

## Discussion

The concept of VV has been extensively studied in recent years. A growing body of experimental evidence suggests the beneficial effects of variable ventilatory modes mimicking physiological variability of the respiratory system [11,13,16,17]. After the introduction of variable pressure-support ventilation (noisy PSV) by our group in 2008 [18], we could demonstrate that the beneficial effects of VV are not only limited to controlled mechanical ventilation but can also be applied during assisted spontaneous breathing [15,19]. Comparing biological variable ventilation and random (noisy) variability using equal amounts of variability, it has been demonstrated that both respiratory patterns yielded comparable effects on lung function. The authors conclude that the amount, but not the pattern, of respiratory variability is crucial for the success of VV [20]. It is worth noting that the variability administered during VV in this study is closely related to the physiological variability of the respiratory system [11,21,22] and has been found to be superior to higher or lower levels of variability in previous experimental studies [23].

Several mechanisms have been proposed to explain the beneficial effects of VV: 1) the *de novo* synthesis of surfactant proteins seems to be enhanced during VV [24,25]; 2) VV seems to recruit previously closed alveolar units [14,26]; 3) the concept of stochastic resonance may explain improvements in respiratory mechanics [17]; and 4) the beneficial effects on gas exchange may be explained by improved ventilation/perfusion matching [18,27].

In the only clinical trial performed with VV in patients undergoing general surgery so far, Boker and colleagues could demonstrate that biological variable ventilation improves gas exchange and respiratory mechanics compared to CV in patients undergoing abdominal aortic aneurysm repair [12]. Their results were confirmed by a small pilot study in eight critically ill patients [28]. The PROVAR study aims at closing the gap between preclinical data and initial clinical application by providing new insights into the perioperative physiological changes due to different intraoperative mechanical ventilation modalities.

This study protocol has several limitations that need to be addressed:

1. The duration of mechanical ventilation may be different across patients due to different lengths of surgery.

2. As part of the clinical routine some patients will receive thoracic epidural anesthesia, whereas others who have contraindications will not; therefore, thoracic epidural anesthesia will be implemented as a covariate in the statistical analysis.

3. Generalizability of the study results is critical since until today there is no commercially available ventilator or anesthesia machine able to perform VV.

4. The anesthesiologist in charge of the intraoperative part of the study cannot be blinded to the ventilator mode; we therefore decided to split personnel for intra- and perioperative analysis in order to have at least the perioperative staff blinded to the ventilator mode.

In conclusion, PROVAR is the first randomized controlled trial aiming at intra- and postoperative effects of VV on lung function. This study may help to define the role of VV during general anesthesia requiring mechanical ventilation.

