## Methods/Design

### Objectives and design

PROVAR is an investigator-initiated, single center, randomized controlled, two-arm trial comparing CV and VV in patients receiving mechanical ventilation during general anesthesia for open abdominal surgery.

The study protocol is approved by the institutional review board of the Medical Faculty and the University Hospital Dresden, Germany (EK 174052011) and has been registered at clinicaltrials.gov (NCT01683578). PROVAR is conducted in accordance with the Declaration of Helsinki and the principles of good clinical practice.

PROVAR tests the hypothesis that intraoperative VV is associated with improved pulmonary function and reduced systemic inflammatory response compared to CV in patients planned for open abdominal surgery. Primary endpoint is the FVC on the first postoperative day. Secondary endpoints are plasma concentrations of interleukin (IL)-6, IL-8 and tumor necrosis factor alpha (TNF-α); partial pressure of oxygen in capillary blood (PcO_2_) on the first postoperative day; peak expiratory flow (PEF) on the first postoperative day; forced expiratory volume in the first second (FEV_1_) on the first postoperative day; oxygenation (PaO_2_/F_I_O_2_) during surgery; changes of spatial distribution of ventilation measured by electrical impedance tomography (EIT); amount of atelectasis measured with magnetic resonance imaging (MRI) on the first postoperative day; and occurrence of postoperative pulmonary complications defined by the modified clinical pulmonary infection score (mCPIS) [9]. Figure 1 shows the CONSORT diagram of PROVAR.

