### Screening, enrollment, randomization and blinding

Investigators screen consecutive patients planned for open abdominal surgery with an expected duration >3 h at the University Hospital Dresden, Germany during regular anesthesiological preoperative evaluations. The screening started in September 2012, and a recruitment time of 24 months has been defined based on the incidence of major abdominal surgery and patient characteristics at our hospital. Demographic data of screened patients are recorded regardless of whether they meet the enrollment criteria. Informed consent is obtained from all patients prior to surgery. All screened patients are reviewed with respect to inclusion and exclusion criteria as summarized in Table 1.

**Table 1 T1:** Inclusion and exclusion criteria for the PROVAR trial

**Inclusion**	**Exclusion**
Patients scheduled for elective open abdominal surgery with expected duration >3 h	Chronic lung disease, except COPD GOLD stage I and II and untreated bronchial asthma
ASA class 2 and 3	Body mass index >40
Expected extubation in the OR	Hypersensitivity or allergy against one of the drugs administered during the study or against drugs with similar chemical structure
Informed consent to participate in the study signed by the patient	Participation of the patient in another clinical trial within the last 4 weeks
	History of substance abuse or any other mental status possibly affecting informed consent
	Pregnancy or breastfeeding
	Women in an age range of possible pregnancy if not:
	• Postmenopausal (12 months of amenorrhea or 6 months of amenorrheawith serum FSH >40 lU/ml)
	• Postoperative (6 weeks after bilateral ovariectomy with or without hysterectomy)
	• Regular and correct use of contraceptives with failure rate of <1% per year
	• Sexual inactivity
	• Vasectomy of sexual partner
	Suspected low patient compliance
	Contraindication for MRI exams
	Mechanical ventilation within the last 30 days

ASA, American Society of Anesthesiologists; OR, operating room; COPD, chronic obstructive pulmonary disease; GOLD, global initiative for chronic obstructive lung disease; FSH, follicle-stimulating hormone; MRI, magnetic resonance imaging.

Randomization is performed by random block randomization with fixed 1:1 randomization ratios within blocks of 2 × 10, 3 × 6 and 3 × 4 patients using closed envelopes.

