### Statistics

Sample size calculation was based on a previous study using FVC as a measure of postoperative pulmonary function following general anesthesia [3]. In the present study, effect size was estimated as 1.086, alpha was defined as 0.05 and power as 0.95. Using a two-tailed Mann–Whitney-*U*-test, sample size calculation yielded 25 patients per group. Analysis was performed using GPower (Software Version 3.1.3, University of Düsseldorf, Germany).

Exploratory analysis will include mean and standard deviation for normally distributed variables. Non-normally distributed variables will be expressed by their medians and interquartile ranges. Categorical variables will be expressed as n (%). Parametrical or non-parametrical tests will be used as appropriate to analyze the data. *P* values for multiple comparisons will be adjusted according to the Bonferroni procedure.

In case of loss to follow-up or consent withdrawal from the trial, the causes will be reported. ITT and per protocol (PP) analysis will be conducted. For the intention-to-treat analysis, data will be processed for all trial patients in the groups in which they were randomized. The PP analysis will be performed as a secondary analysis if there are a considerable number of patients who do not receive study therapy or are lost to outcome assessment. Missing data will be handled by means of the last observation carried forward method.

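### The promised epidural covariate does not fit the unadjusted Mann–Whitney test used for sizing, and no adjusted primary analysis of day-1 FVC is named

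*Protocol article*

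**What the plan says.** Four statements in the protocol article bear on the primary analysis.

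- Objectives and design: "Primary endpoint is the FVC on the first postoperative day".
- Statistics, sample size: "effect size was estimated as 1.086, alpha was defined as 0.05 and power as 0.95". The test is given with "Using a two-tailed Mann–Whitney", and the "sample size calculation yielded 25 patients per group".
- Statistics, analysis: "Parametrical or non-parametrical tests will be used as appropriate to analyze the data". No test is tied to FVC, no criterion for the choice is given, and no covariate is mentioned.
- Discussion, second limitation: epidural use will differ between patients, depending on contraindications, and the remedy offered is adjustment: "therefore, thoracic epidural anesthesia will be implemented as a covariate in the statistical analysis". No model and no endpoint is named.

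Randomization is described as "fixed 1:1 randomization ratios within blocks of 2 × 10, 3 × 6 and 3 × 4 patients using closed envelopes", with no stratification by epidural. Baseline spirometry is taken at visit 1 (Time course of interventions/study protocol).

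**The concern.** The authors see epidural use as a source of variation in outcome and choose a statistical remedy for it. That remedy appears only among the limitations. The section that should carry it refers to one unadjusted rank test, for sizing, and to an open choice of test. An analyst who takes the sizing test as the primary analysis drops the covariate. An analyst who keeps the covariate runs a model that is described nowhere.

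Two things are at stake. The first is that the primary p-value has no single stated definition. The second is power: if epidural status moves FVC by a sizeable fraction of an SD, an unadjusted test leaves that variation in the error term. With no stratification described, adjustment is the only stated means of dealing with it.

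**Working it through.** **1. Reproduce the stated sample size.** Inputs from Statistics: d = 1.086, two-sided alpha 0.05, power 0.95. Use the noncentral t distribution with the Mann–Whitney asymptotic relative efficiency for a normal parent, 3/π.

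- Effective size per group: 25 × 3/π = 23.87.
- Noncentrality: 1.086 × √(23.87/2) = 3.752.
- Degrees of freedom: 2 × 23.87 − 2 = 45.75; critical t = 2.013.
- Power: 0.957 with 25 per group and 0.949 with 24.

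So 25 per group is exactly right for the test named.

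**2. Which analyses satisfy both sections?**

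| Analysis of day-1 FVC | Allowed by Statistics | Carries the epidural covariate |
|---|---|---|
| Mann–Whitney U | yes | no |
| t-test | yes | no |
| Linear model with epidural | yes (parametric) | yes |
| Rank ANCOVA or stratified rank test | yes (non-parametric) | yes |

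Only the last two rows meet both statements, and the article names neither.

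**3. Power at the planned effect.** The article gives neither the proportion with an epidural nor its effect on FVC, so these are assumptions: use 50% or 70%, effect 0.5 or 1.0 SD. The correlation of baseline with day-1 FVC is assumed to be 0.5 or 0.7. Errors are normal, with SD 1 within epidural groups, and 1.086 is taken on that SD. There are 25 per arm and 20,000 simulated trials per scenario.

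| Epidural use, effect | Mann–Whitney | Linear model, arm + epidural | + baseline FVC, r = 0.5 | + baseline FVC, r = 0.7 |
|---|---|---|---|---|
| 50%, 0.5 SD | 0.940–0.942 | 0.960–0.962 | 0.988 | 0.999 |
| 50%, 1.0 SD | 0.896 | 0.960 | 0.989 | 0.999 |
| 70%, 0.5 SD | 0.943–0.944 | 0.958–0.961 | 0.988 | 0.999 |
| 70%, 1.0 SD | 0.909–0.911 | 0.960–0.961 | 0.988 | 0.999 |

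A hand check explains the pattern. Ignoring an epidural effect b with use p raises the SD to √(1 + p(1 − p)b²). For p = 0.5 and b = 1.0 this is √1.25 = 1.118, so the effect shrinks to 1.086/1.118 = 0.971 and the method of step 1 gives 0.907. Adding baseline FVC with r = 0.5 shrinks the residual SD to √(1 − 0.25) = 0.866; the effect becomes 1.086/0.866 = 1.254, and a noncentral t with 46 degrees of freedom gives 0.991.

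The scale matters. If 1.086 is instead on the total SD, Mann–Whitney keeps roughly the 0.957 of step 1. For p = 0.5 and b = 1.0, the within-epidural effect is then 1.086 × 1.118 = 1.214, with adjusted power of about 0.988. The adjusted model is ahead on either scale, but only the first puts Mann–Whitney below 0.95.

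**4. Type I error, same assumptions, no treatment effect.** Each analysis fixed in advance rejects in 0.044–0.053 of trials. Reporting whichever of Mann–Whitney, t-test and epidural-adjusted model is significant rejects in 0.067–0.079.

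**The case against.** The strongest reply is that the article contains no contradiction. Mann–Whitney is declared only for sizing. Sizing on an unadjusted test and then analysing with adjustment is ordinary practice. Parametric and non-parametric methods both include versions that carry a covariate, so both sections can be followed at once. The model form is commonly left to an analysis plan, and none is shown here.

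Much of this stands, and it rules out four stronger readings that a reader might infer:

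- *The two sections are incompatible.* They are not; an adjusted linear or rank model satisfies both.
- *The test will be chosen after the results are seen.* The article does not say so. Its summary statistics depend on normality, so distribution is the natural criterion. With a normality check choosing between t-test and Mann–Whitney, simulated type I error was 0.051–0.052; choosing between ANCOVA and rank ANCOVA gave 0.050–0.052.
- *Type I error is inflated to about 0.07–0.08.* That requires reporting the smallest of three p-values, which nothing in the plan proposes. Nor does chance imbalance in epidural use inflate it: under randomization the unadjusted test stays near 0.05.
- *The sample size is wrong.* It is reproduced, and it is enough for the adjusted model.

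The reply does not dispose of the point. The article does more than omit a detail. It makes a firm commitment to a covariate, and the only test it names cannot honour that commitment. It also leaves open whether the adjusted analysis is the primary one.

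**Conclusion.** The concern holds as a fault of specification. The sizing test and the covariate commitment can be reconciled only by an adjusted model, and the article does not name one for day-1 FVC. A clearly better primary analysis is available from data already being collected. Under the assumptions in the working, power rises from about 0.90–0.95 (Mann–Whitney) to about 0.96 with epidural and about 0.99 or more with baseline FVC, with N unchanged.

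The power figures depend on assumed epidural use, epidural effect and baseline correlation, on normal errors, and on 1.086 being measured on the within-epidural SD. The mismatch between sections, and the fact that the sizing test has no covariate term, depend on none of these.

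**What to change.** In Statistics, state one primary analysis: a linear model of day-1 FVC on arm, thoracic epidural (yes/no) and baseline FVC from visit 1, tested two-sided at 0.05. If a rank method is preferred, name rank ANCOVA with the same terms. Make the unadjusted Mann–Whitney and t-tests sensitivity analyses, and limit the open choice of test to other endpoints. Move the epidural commitment from the limitations into this paragraph, and define when epidural status is recorded, since the article gives no timing relative to allocation.

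Baseline FVC goes beyond what the article promises; it is proposed for its gain in precision. The sample size paragraph can stay, with a sentence saying that 25 per group is also sufficient for the adjusted model.

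The cost is wording only: no added patients, visits or measurements, provided epidural status is recorded in the case report form. Enrollment has begun, so the text should be settled before any outcome data are examined by arm.

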## Trial status

Enrollment has begun.

## Abbreviations

AE: adverse event; CRF: case report form; CV: conventional lung protective ventilation; DMSB: Data Safety and Monitoring Board; EIT: electrical impedance tomography; FEV1: forced expiratory volume in the first second; FVC: forced vital capacity; GCP: good clinical practice; IL: interleukin; ITT: intention to treat; mCPIS: modified clinical pulmonary infection score; MRI: magnetic resonance imaging; PaO2/FIO2: ratio of arterial partial pressure of oxygen and inspired oxygen fraction; PcO2: partial pressure of oxygen in capillary blood; PEEP: positive end-expiratory airway pressure; PEF: peak expiratory flow; PP: per protocol; PROVAR: The PROtective VARiable ventilation trial; SAE: severe adverse event; TNF-α: tumor necrosis factor alpha; VV: variable lung protective ventilation.
